**Telemedicine can facilitate delivery of HCV treatment to rural areas with a shortage of treating clinicians.** Although our original application proposed to adapt elements from two telemedicine models to provide support for local primary care clinicians to care for PWIDs, our work in the UG3 phase and in preparation for the UH3 has found limited willingness and bandwidth of local primary care providers to provide HCV care to persons who are actively injecting drugs. Instead, we propose to provide direct teleconsultation and treatment for HCV among PWIDs in collaboration with local harm reduction agencies. We propose to use a mobile van because of severe space constraints within these agencies, and as a means to facilitate outreach to areas poorly served by brick-and-mortar services. Evidence supports that telehealth treatment for HCV can achieve equivalent or better outcomes than typical referral for face-to-face consultation in rural areas, but significantly reduces the time to a completed consultation from over two weeks to less than one day, with high rates of satisfaction and greater rates of therapy completion.

In our UG3 qualitative interviews, nearly all stakeholders viewed telehealth interventions as opportunities to reduce the distances traveled by patients in rural, mountainous, hard-to-reach locations, and increase access to needed services in “treatment deserts”, where there are few Interstates, highways, and a lack of paved

roads. Even in places where Hub and Spoke models have demonstrated great success, it can be challenging for patients to get to their appointments. As two public health officials described:

...we have folks who really just cannot...access treatment...without taking an hour-long bus ride both ways.

...it's hard to get around...There's... only...two interstates in a tiny fraction of this state, and most of this state is not covered by major roads...and we have a lot of weather here and a big mountain range in the middle ... And so it can be really hard for people to get access to care, and we don't have a lot of highly trained...specialty providers.

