### E. Analysis Plan.

**Primary outcomes** will be the proportion of PWID who initiate DAA treatment, achieve sustained virologic response at 12-weeks post-treatment (SVR12), and report no syringe sharing in the prior 30 days at follow-up. We hypothesize that, compared with EUC, mobile tele-HCV care will be associated with:

H1: higher rates of DAA treatment initiation,

H2: higher rates of sustained virological response 12-weeks post treatment (SVR12 or cure), and

H3: lower rates of syringe sharing behavior among rural HCV-infected PWIDs

Secondary outcomes will include HBV and HAV vaccination series completion rates, initiation of MOUD and ED visits, as well as health-related quality of life (HRQOL) and substance use.

**Preliminary Analyses:** Initial data analysis will describe the distribution of all outcomes by study group. Continuous measures will be reported using means, standard deviations, medians and percentiles. Categorical measures will be reported using frequencies and percentages. Rather than testing for baseline covariate imbalance, stratified analyses will be conducted for baseline covariates that are known to be strongly associated with outcomes, as well as those that show imbalance on inspection.

**Primary outcome analyses.** We will apply ICH-E9 guidelines for statistical analysis and the CONSORT statement for reporting of findings. Since Aims 1 and 2 examine the effectiveness of the intervention by comparing proportions in the two study groups, we will apply the same statistical approach. For the univariable approach, study groups will be compared using Pearson's chi-square or Fisher's exact test. Stratification and adjustment for relevant baseline covariables will be accomplished with logistic regression. In

these models, study group and other categorical measures will be represented with indicator variables. Continuous explanatory variables will be evaluated to verify linearity of their logit and, if not, they will be rescaled. Model fit will be examined and final results will be expressed as odds ratios and adjusted proportions each with 95% confidence intervals. Significance testing will be conducted at a critical level of 5%.

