For treatment initiation, we expect 50% or fewer participants in the EUC to initiate treatment, and the MTC intervention to improve initiation to at least 70%. Thus, 220 individuals randomized equally to two groups would provide 86% power to detect a 20% absolute difference between study groups for a test of difference in proportions at  $P < .05$ . This difference is equivalent to an odds ratio of 2.33, or a medium effect size.

For sustained viral response at 12 weeks post-treatment (SVR12), an intent-to-treat approach would include all participants randomized. We expect the success rates to be lower than for the "as-treated" approach, since attrition may occur both at initiation of therapy, as well as completion of therapy. Thus a sample of 110 participants per group would provide about 80% power to detect difference in the proportion of treatment success of 30% in the EUC and 48.5% in the MTC group. This difference is equivalent to an odds ratio of 2.12, which is equivalent to a medium effect size (approximate Cohen's  $d = 0.42$ ). Because the lower treatment initiation rate in the EUC group will favor the MTC group, we also present an as-treated sample size calculation. We expect about 55 patients (i.e., 50% of 110) in the EUC group and at least 77 patients (70% of 110) in the MTC to initiate treatment. Again, we expect the MTC intervention to overcome substantial obstacles to achieving SVR12. As such, a difference in the proportion of participants achieving SVR12 at least as large as 25% is expected. Thus a sample of 132 participants (55 in usual care and 77 in intervention), would provide about 82% power to detect a difference between the MTC intervention and EUC groups of 25% absolute difference (i.e., 65% vs. 40%) for a test of difference in proportions at a critical level of 5%. This difference is equivalent to an odds ratio of 2.79, which is about a medium effect size (equivalent to Cohen's  $d$  of 0.56)

For injection sharing behavior, our UG3 survey found that 77% of HCV-infected PWIDs shared *any* equipment in the 30 days prior, and 66% shared syringes. Using an ITT approach, a sample of 110 participants per group would provide at least 80% power to detect a 19% or greater reduction in sharing behaviors for

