either measure (i.e., 77% vs. 58% for sharing any equipment, and 66% vs. 47% for sharing syringes only) for a two-sided test in the difference in proportions at a critical level of 5%. The 19-point difference for these outcomes yields an OR of about 2.4, which equates to a medium effect size (approximate Cohen's  $d = 0.48$ ).

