#### **6. Trial stopping rule.**

Early termination for efficacy is based on the difference between study groups on the proportion achieving SVR12. It is computed using the O'Brien-Fleming estimate of the alpha-spending function for one interim (at

50% at 12-weeks post-treatment) and one final test of significance. At the interim look, if the difference in proportion of completing treatment achieves a p-value of 0.003 or less, enrollment will stop due to efficacy. If the study continues to completion, the final p-value for testing adjusted for the interim look will be 0.047. At the interim look, we will also consider stopping for futility. This decision will be based on conditional power (Proschan, Lan, Wittes, 2010). Using the interim data, conditional power will be computed under two conditions: a) conditional power under the originally-hypothesized estimates, and b) conditional power under the observed data. If both estimates of conditional power fall below 0.10, then then we consider stopping the study for futility. While a low conditional power will inform the decision to stop the study, the final decision to terminate the trial will consider other factors, such as participant engagement and care delivery.

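### The SVR12 planning rates do not fit together: the plan's own initiation and as-treated rates give 20% vs 45.5% by intent-to-treat, not the stated 30% vs 48.5%

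*Protocol*

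**What the plan says.** All the rates stand in the sample-size paragraphs of the Protocol's Analysis Plan (section E).

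- **Initiation (H1):** at most 50% in EUC and at least 70% in MTC, with 86% power at 220 randomized 1:1.
- **SVR12, intent-to-treat (H2):** all randomized participants count. Success is expected to be lower than as-treated because of attrition at initiation and completion. From this the text concludes that 110 per group gives about 80% "power to detect difference in the proportion of treatment success of 30% in the EUC and 48.5% in the MTC group", with an odds ratio of 2.12.
- **SVR12, as-treated:** offered because lower EUC initiation is said to favor MTC. "We expect about 55 patients (i.e., 50% of 110) in the EUC group and at least 77 patients (70% of 110) in the MTC" group to start treatment. A difference of at least 25 points is expected among them, and about 82% power is claimed for a "25% absolute difference (i.e., 65% vs. 40" percent.

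The Trial stopping rule (Data and Safety Monitoring, E.6) bases one of its two futility criteria on "conditional power under the originally-hypothesized estimates". It does not say which SVR12 pair that is.

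**The concern.** The section on determining SVR12 (F) defines it from a venous sample taken twelve weeks after treatment completion. A participant who never starts treatment therefore cannot reach it. The intent-to-treat rate in each arm must equal the initiation rate times the SVR12 rate among initiators, but the three pairs in the sample-size text do not obey that identity.

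SVR12 is a primary outcome and the only one on which the trial can stop early. A reader should be able to trace its power statement, and the benchmark for its futility calculation, to one set of assumptions.

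**Working it through.** **Inputs.** 110 per arm; initiation 50% and 70%; SVR12 among initiators 40% and 65%; intent-to-treat SVR12 30% and 48.5%; as-treated groups of 55 and 77 (all from section E). The test is taken as two-sided at 5%. The text says so for syringe sharing ("two-sided test in the difference in proportions at a critical level of 5" percent); I assume the same for SVR12.

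**Power formula** (z test, pooled variance under the null): power = Φ{[|p2 − p1| − 1.96·√(p̄(1−p̄)(1/n1+1/n2))] / √(p1(1−p1)/n1 + p2(1−p2)/n2)}.

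**1. Reproduce the plan's figures.**
- 30% vs 48.5%, 110 per arm: (0.185 − 1.96×0.0658)/0.0647 = 0.865, so power is 80.7% (stated: about 80%). At the final 0.047 level it is 79.9%.
- 40% vs 65%, 55 vs 77: (0.25 − 1.96×0.0879)/0.0855 = 0.908, so 81.8% (stated: about 82%).
- 50% vs 70%, 110 per arm: 86.2% (stated: 86%).

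**2. Multiply the plan's own rates.**
- EUC: 0.50 × 0.40 = 20.0% (22 of 110). With initiation at most 50%, this is a ceiling.
- MTC: 0.70 × 0.65 = 45.5% (50 of 110).
- Power for 20% vs 45.5% at 110 per arm: (0.255 − 1.96×0.0633)/0.0609 = 2.15, so 98.4%.

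**3. Solve back for initiation.**
- EUC: 30/40 = 75.0%, against at most 50%.
- MTC: 48.5/65 = 74.6%, compatible with at least 70%.

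**4. Solve back for SVR12 among initiators.**
- EUC: 30/50 = 60.0%. MTC: 48.5/70 = 69.3%.
- The gap is 9.3 points. It is the largest possible, since lower EUC initiation raises the 60% and higher MTC initiation lowers the 69.3%. The plan expects at least 25.
- As-treated power at 60% vs 69.3%, 55 vs 77: (0.0929 − 1.96×0.0840)/0.0844 = −0.85, so 19.8%.

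**5. Check the direction.** Lower EUC initiation is said to favor MTC by intent-to-treat, yet the planned intent-to-treat gap (48.5 − 30 = 18.5 points) is smaller than the as-treated gap (25 points).

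**6. Odds ratio for 30% vs 48.5%.** (0.485/0.515)/(0.30/0.70) = 0.942/0.429 = 2.20, not 2.12.

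**7. Effect on the futility limb.** Take the look at half the information (t = 0.5, 55 per arm) and the final level from the stopping rule ("the final p-value for testing adjusted for the interim look will be 0.047", so c = 1.986). Conditional power = Φ{[Z√t + θ(1−t) − c]/√(1−t)}, where θ is the expected final z. Setting it to 0.10 gives Z = [c − 0.5θ − 1.2816×0.7071]/0.7071.

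| Pair | θ | Z at CP = 0.10 | SE at interim | MTC minus EUC |
|---|---|---|---|---|
| 30% vs 48.5% | 0.185/0.0647 = 2.86 | −0.50 | 0.0647×√2 = 0.0914 | −4.5 points |
| 20% vs 45.5% | 0.255/0.0609 = 4.19 | −1.43 | 0.0609×√2 = 0.0861 | −12.3 points |

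With c = 1.96 the Z values are −0.53 and −1.47, or −4.8 and −12.7 points. Conditional power under the observed data falls below 0.10 at Z below 0.76, so the hypothesized limb is the one that binds.

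**The case against.** **It is only a minimum detectable difference.** The text speaks of power to detect, and 48.5% looks like a value solved for 80% power. A detectable gap need not equal the product of other expectations. This has some force, but the pair is introduced as following from the expected loss at initiation and completion. Even a detectable difference needs a control rate, and 30% exceeds the 20% ceiling set by the same text.

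**Untreated participants might have undetectable RNA.** Reaching 30% of 110 = 33 EUC successes would need 33 − 22 = 11 of the 55 non-initiators, or 20%. No such assumption is stated, the trial seeks untreated chronic infection, and SVR12 is defined after treatment.

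**The power figure is right and the discrepancy is conservative.** Both points stand. The power arithmetic is sound, and the plan's own product gives more power.

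**Stronger readings that the document does not support.**
- A reader might infer that H2 assumes equal initiation, because the back-solved rates are 75.0% and 74.6%. The text says the reverse about initiation, and the MTC figure fits at least 70%. Only EUC strictly conflicts.
- A reader might infer that H2 is underpowered. The Background says that "telehealth treatment for HCV can achieve equivalent or better outcomes than typical referral", and with equal SVR12 among starters and 50%/70% initiation the power would run from 28% (40% SVR12 among starters) to 77% (90%). The plan does not assume equality. It expects at least 25 points among starters, and the same Background sentence goes on to report better therapy completion.
- A reader might call the futility benchmark undefined. Only one intent-to-treat pair is printed, so 30% vs 48.5% is the natural reading. The difficulty is that the plan's other rates yield a second one.

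**Conclusion.** The planning rates for SVR12 contradict each other. Given the plan's initiation and as-treated rates, intent-to-treat SVR12 is 20% vs 45.5% with about 98% power. Given its intent-to-treat and initiation rates, the as-treated contrast is at most 60% vs 69%, with about 20% power. The 80% and 82% claims are each correct for their own inputs, but those inputs cannot both hold with the stated initiation.

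This rests on SVR12 requiring treatment and on a two-sided 5% test. It does not show the trial to be too small for H2.

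The futility consequence is secondary. The hypothesized limb moves from about 5 to about 12 to 13 points in EUC's favor depending on the pair, assuming half the information and 55 per arm. Both conditional powers must be below 0.10, and the rule only informs a decision that weighs other factors too.

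**What to change.** Keep n = 220 and amend the text.

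1. Choose one initiation pair and one SVR12-among-initiators pair, derive the intent-to-treat pair as their product, and restate both SVR12 power figures. Alternatively, label 30% vs 48.5% explicitly as a minimum detectable difference and reconcile its 30% control rate with the other rates.
2. If 30% vs 48.5% stays, correct its odds ratio to 2.20 and the matching effect size (ln 2.20/1.81 ≈ 0.43, not 0.42).
3. Name the chosen intent-to-treat pair in the Trial stopping rule, before any interim data are seen.

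A power row assuming equal SVR12 among starters would be a reasonable optional sensitivity case, but it is not needed to correct the error. The cost is a revised paragraph and one clause, with no added participants and no change to the primary analysis.

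### The SVR12 planning rates for all randomised participants and for treatment initiators do not fit the protocol's own initiation rates, mainly in the EUC arm, so the stated 80% and 82% powers cannot both hold

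*Protocol*

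**What the plan says.** All the planning figures stand together in the sample-size text of the protocol's Analysis Plan (section IV.E).

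- **Initiation:** "we expect 50% or fewer participants in the EUC to initiate treatment, and the MTC intervention to improve initiation to at least 70" per cent.
- **SVR12, all randomised:** "an intent-to-treat approach would include all participants randomized", and 110 per group give about 80% power for a "difference in the proportion of treatment success of 30% in the EUC and 48.5% in the MTC group". The text adds: "This difference is equivalent to an odds ratio of 2.12", with d of about 0.42.
- **Link between the two analyses:** "We expect the success rates to be lower than for the 'as-treated' approach, since attrition may occur both at initiation of therapy" and at completion of therapy.
- **SVR12, as-treated:** "We expect about 55 patients (i.e., 50% of 110) in the EUC group and at least 77 patients (70% of 110) in the MTC" are expected to initiate. An advantage of at least 25 points is expected among them, and the sample "would provide about 82% power to detect a difference between the MTC intervention and EUC groups of 25% absolute difference (i.e., 65% vs. 40" per cent.

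The futility rule in the Data and Safety Monitoring part (section E.6, Trial stopping rule) depends on these figures, because one of its two criteria is "conditional power under the originally-hypothesized estimates".

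**The concern.** The three sets of figures describe the same 220 people. The as-treated group sizes are taken directly from the initiation rates, so the protocol itself ties the sets together. SVR12 is measured 12 weeks after treatment ends (section IV.F), so someone who never starts treatment would ordinarily count as a failure in the all-randomised analysis. The all-randomised rate is then the initiation rate multiplied by the rate among initiators. The stated figures do not satisfy this relation.

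SVR12 is one of three primary outcomes and the only one that drives the interim rule. If its planning assumptions contradict each other, a reader cannot tell which effect the trial was designed around, and at least one of the two quoted powers does not describe the design.

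**Working it through.** **Inputs** (all from the sample-size text): initiation 50% EUC and 70% MTC; all-randomised SVR12 30% and 48.5%, n = 110 per group; as-treated SVR12 40% and 65%, n = 55 and 77. Alpha is 5%. Two-sided testing is stated only for the sharing outcome, but it also reproduces the SVR12 figures.

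**Power formula** (two proportions, pooled variance under the null):

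power = Φ{ [ |p2 − p1| − 1.96·√( p̄(1 − p̄)(1/n1 + 1/n2) ) ] / √( p1(1 − p1)/n1 + p2(1 − p2)/n2 ) }

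**Step 1. Reproduce the stated powers.**
- Initiation, 50% vs 70%, 110 per group: 86.2% (stated 86%).
- All randomised, 30% vs 48.5%, 110 per group: (0.185 − 0.1291)/0.0647 = 0.865, power 80.7% (stated about 80%).
- As-treated, 40% vs 65%, 55 and 77: (0.25 − 0.1723)/0.0855 = 0.908, power 81.8% (stated about 82%).

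None of the three powers is miscalculated.

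**Step 2. From as-treated to all randomised.**
- EUC: 0.50 × 40% = 20.0%, stated 30%.
- MTC: 0.70 × 65% = 45.5%, stated 48.5%.
- Power for 20.0% vs 45.5%, 110 per group: (0.255 − 0.1240)/0.0609 = 2.151, or 98.4%.

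**Step 3. From all randomised to as-treated.**
- EUC: 30% / 0.50 = 60.0%, stated 40%.
- MTC: 48.5% / 0.70 = 69.3%, stated 65%.
- The difference is 9.3 points (odds ratio 1.50), not 25.
- Power with 55 and 77: (0.0929 − 0.1646)/0.0844 = −0.850, or 19.8%. An exact enumeration of the chi-square test gives 19.9%.

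| Set kept | All randomised | Power | Among initiators | Power |
|---|---|---|---|---|
| All-randomised pair | 30% / 48.5% | 80.7% | 60% / 69.3% | 19.8% |
| As-treated pair | 20% / 45.5% | 98.4% | 40% / 65% | 81.8% |

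**Step 4. Which arm fails?** The initiation that reconciles both stated SVR12 rates is 30/40 = 75% in EUC and 48.5/65 = 74.6% in MTC. The MTC figure is compatible with a planning value of at least 70%. The EUC figure is not compatible with a value of at most 50%. This pair would also remove the 20-point initiation difference on which H1 is powered.

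**Step 5. Sensitivity.**
- A lower EUC initiation does not help. At 40% in EUC and 70% in MTC, the all-randomised rates imply 30/40 = 75% vs 69.3% among initiators, which reverses the direction.
- Suppose a share c of non-initiators counted as successes. The implied rates among initiators become 60% − c and (48.5% − 0.3c)/0.7. As-treated power is then 23% (c = 2%), 29% (5%), 41% (10%) and 65% (20%), still below 82%.

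**Step 6. Odds ratio.** (0.485/0.515)/(0.30/0.70) = 2.20, against the stated 2.12. Then d = ln(2.20)/1.81, about 0.43, against 0.42.

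**The case against.** The best defence is that nothing is miscalculated: both SVR12 powers reproduce. The all-randomised pair is worded as a difference the sample can detect, whereas the 25-point as-treated gap is what the protocol expects. The 48.5% may simply be the smallest rate detectable at about 80% power (an inference, as the protocol does not say so). On that reading the 30% is a cautious EUC value and the trial has power to spare. This stands in part. It removes any claim of a sample-size shortfall, but it does not make 30% attainable in EUC with at most half initiating and 40% of those succeeding.

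Three stronger readings are tempting and are not supported:

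- **A reader might infer that the true as-treated power is 20%, or that SVR12 is underpowered.** The 20% follows only if the all-randomised pair is kept. If the as-treated pair is kept, the 82% stands and the all-randomised power rises to 98%. The protocol does not rank the two.
- **A reader might infer that the futility rule could give opposite decisions.** With a final critical value of 1.986 (p = 0.047) and an interim Z of −0.6, conditional power is about 0.08 for 18.5 points and 0.29 for 25.5 points, on either side of the 0.10 limit. But the protocol never states 25.5 points; it is derived in Step 2. The two readings differ only for interim Z from about −1.3 to −0.5, a trend against MTC. That has a probability below 1% if the 18.5-point effect is true, and somewhat over 20% if there is no effect. The rule is also non-binding: both conditional powers must be low, and other factors then enter. What remains is an unnamed input, not a demonstrated wrong decision.
- **A reader might infer that the as-treated comparison is a second confirmatory test of H2.** The text puts the all-randomised analysis first and offers the as-treated figure as an additional calculation, whose 5% is simply the alpha of that calculation.

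**Conclusion.** The SVR12 planning rates contradict each other, and the fault lies mainly in the EUC arm. The stated 80% and 82% are each correct for their own inputs but cannot both hold under one set of assumptions. They become either about 80% and 20%, or about 98% and 82%. This rests on initiation of 50% and 70% and on non-initiators counting as failures; relaxing the second assumption to 20% spontaneous success narrows the gap but does not close it. No shortfall in the all-randomised comparison is shown. The odds ratio of 2.12 is a separate small slip that changes no power or sample size.

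**What to change.** In the sample-size text, adopt one consistent set of initiation, as-treated and all-randomised SVR12 rates, and restate the powers that follow. The choice is the sponsor's:

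- If 30% and 48.5% of all randomised are kept, the rates among initiators are 60% and 69.3%. As-treated power is then about 20%, and the 82% should be removed or restated.
- If 40% and 65% among initiators are kept, the all-randomised rates are 20% and 45.5%, with about 98% power.

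In the stopping rule, name the all-randomised SVR12 difference that serves as the hypothesised effect for conditional power. Describe the as-treated comparison as supportive: it conditions on initiation, which the intervention is meant to change, so it is not protected by randomisation. Correct the odds ratio for 30% versus 48.5% to 2.20 (d about 0.43).

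The cost is a revision of text. It needs no additional participants, visits or data. If the all-randomised pair is kept, the protocol must also accept a much less favourable as-treated figure.
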